### Randomization and concealment

Prior to study initiation, an independent researcher who has no contact with any participant will use SAS 9.4 software (SPSS Inc., Chicago, IL, USA) to generate a blocked random number table (block size = 4) to divide eligible participants in a 1:1 ratio into either the tTXA or ivTXA group. Both the participants’ ID numbers and their respective treatment groups (tTXA or ivTXA) will then be sealed in an envelope and made available only to an appointed nurse who is uninvolved in the study conduction.

Participants and researchers will all be blinded to the group allocation. However, at any time point during or after surgeries, any clinician can be “unblinded” to a patient’s treatment group in case of an apparent or suspected medical emergency. A copy of the consent form will be placed inside every chart, and there will also be a note on the front cover of the chart informing that the patient is enrolled in the study, along with contact numbers of the researchers.

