### Study setting and investigators

This trial will be conducted at a single tertiary care teaching hospital. The study settings include the wards and the operating rooms of the orthopedic department (200 beds) at this comprehensive hospital (2500 beds). All the laboratory indices in this study will be tested in the key labs of the teaching hospital.

Participants will be recruited through the outpatient clinic of one investigator, and will be consented by the investigators. All the investigators possess working experience in clinical orthopedic research projects. The surgeries will be conducted by a single team of surgeons who have completed clinical fellowship in spinal surgery.

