### Adverse event management and emergency termination of the study

In this study, AEs include, but are not limited to, deep venous thrombosis, myocardial infarction, pulmonary embolism, cerebrovascular disease, impaired liver function, impaired renal function, incisional hematoma/infection, and convulsive seizures. Patients will be closely monitored during the study period. In case of suspicions for the preceding AEs, the study team will break the blind, and patients will be treated appropriately under the instructions of both spine surgeons and internal medicine physicians. All AEs will be diligently recorded and reported in the final manuscript.

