### Trial status

The study is currently recruiting participants. Important protocol amendments will be communicated to relevant bodies (investigators, IRBs, journals) by [name], trial principal investigator, as soon as changes are made.

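### A single fixed block size of 4, published while one clinic is still recruiting, lets each broken code give partial information on up to three other allocations

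*Protocol article*

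**What the plan says.** Under Randomization and concealment, an independent researcher is to "generate a blocked random number table (block size = 4) to divide eligible participants in a 1:1 ratio". The section mentions no stratification and no second block size. Identifiers and groups "will then be sealed in an envelope and made available only to an appointed nurse who is uninvolved in the study conduction".

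Under Study setting and investigators: "This trial will be conducted at a single tertiary care teaching hospital". Also: "Participants will be recruited through the outpatient clinic of one investigator, and will be consented by the investigators". One team of surgeons operates.

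The article is dated 12 February 2019, and Trial status says: "The study is currently recruiting participants". The block size therefore became public during recruitment.

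Two rules make allocations known during the trial. Randomization and concealment lets any clinician learn one patient's group in an actual or suspected emergency. Adverse event management goes further: when a listed event is suspected, "the study team will break the blind". The list includes impaired liver function and incisional hematoma or infection as well as rarer events such as seizure.

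**The concern.** In a well-blinded trial a small fixed block does little harm, because past allocations stay hidden. Here the plan provides for some of them to become known, and to the study team itself. With every block equal to 4 and that fact published, anyone who can follow the order of enrolment can carry what was learned about one patient over to that patient's block-mates. One hospital, one clinic and one surgical team make the order easy to follow.

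Several judgements could be affected by a guess at the arm:

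- who is booked next, within an unstratified range of 3 to 5 fusion levels;
- whether bleeding during surgery counts as unexpected and massive, which excludes the participant (Participants) and, because the ITT set requires all eligibility criteria to be met, could remove that patient from the primary analysis;
- transfusion, whose volume is added to total blood loss (Secondary outcomes);
- the assessment of visible loss, which also feeds hidden blood loss.

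**Working it through.** The plan states no predictability figure, so there is none to reproduce.

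**Inputs from the protocol:** block size 4; 1:1 allocation, so two patients per arm in each block; 176 patients, so 176/4 = 44 whole blocks.

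**Assumptions, not in the protocol:** each patient's code is broken independently with probability p = 0.05, 0.10 or 0.20; earlier block-mates have been unblinded by the time the next patient enrols; list order follows enrolment order, so block boundaries are known.

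**Within one block** there are six equally likely arrangements.

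- One code known: three patients remain, two of them in the opposite arm. Each block-mate moves from 1/2 to 2/3. None becomes certain.
- Two codes known: they agree with probability 1/3, and then the other two patients are certain. If they differ, the other two are back at 1/2.
- Three codes known: the fourth is certain.
- A break at a random position has at least one later block-mate with probability 3/4, and on average (3+2+1+0)/4 = 1.5 of them.

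**Chance that a patient is partly predictable at enrolment, by position in the block**

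- Position 1: 0
- Position 2: p
- Position 3: 2p(1−p) + p²/3
- Position 4: 3p(1−p)² + p²(1−p) + p³

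**Expected gain in correct guesses.** A 2/3 guess gains 2/3 − 1/2 = 1/6 over a coin toss, and a certain one gains 1/2.

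- Position 2: p/6
- Position 3: 2p(1−p)/6 + p²/6
- Position 4: 3p(1−p)²/6 + [p²(1−p) + p³]/2

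| p | Predictable at positions 2, 3, 4 | Mean over 4 positions | × 176 | Gain at positions 2, 3, 4 | Mean over 4 positions | × 176 |
|---|---|---|---|---|---|---|
| 0.05 | 0.050, 0.096, 0.138 | 0.071 | 12 | 0.0083, 0.0163, 0.0238 | 0.012 | 2.1 |
| 0.10 | 0.100, 0.183, 0.253 | 0.134 | 24 | 0.0167, 0.0317, 0.0455 | 0.023 | 4.1 |
| 0.20 | 0.200, 0.333, 0.424 | 0.239 | 42 | 0.0333, 0.0600, 0.0840 | 0.044 | 7.8 |

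**If boundaries are not known.** After one break, the next patient is in the same block with probability (B−1)/B and is then in the opposite arm with probability (B/2)/(B−1). Otherwise the chance is 1/2. The sum is 1/2 + 1/(2B).

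- Fixed B = 4: 1/2 + 1/8 = 0.625.
- Sizes 4, 6 and 8 drawn equally often, so that patients fall in them in proportions 4/18, 6/18 and 8/18: 1/2 + 3 × 1/36 = 0.583.

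For a patient known to share a block with the unblinded one, the chance is 0.667 for blocks of 4, 0.600 for 6 and 0.571 for 8.

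**The case against.** The case for leaving the plan alone has weight. Both arms receive all three solutions, with saline replacing drug where needed, so past allocations are not routinely visible. The list comes from someone without participant contact. The primary outcome rests mainly on hematocrit, height and weight, which a guess at the arm can hardly move. The leak from the block alone is probabilistic, stops at three block-mates and reaches unenrolled patients only when the block is unfinished. The unblinding rates are assumed. Varying blocks lower the next-patient figure only from 0.625 to 0.583. All of this stands, and it limits the size of the point. It does not remove it, because unblinding by the study team is written into the plan.

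Four stronger readings are tempting, and the document does not support them.

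- **One break exposes every allocation.** A reader might infer a single envelope holding the whole list. The wording also fits one envelope per participant, access is limited to the nurse, and unblinding concerns one patient's group. Full exposure follows only under the first reading.
- **Emergency unblinding cannot work.** The chart note is issued "along with contact numbers of the researchers", who are blinded, while the nurse holds the code. Blinded contacts could call the nurse, and an article commonly leaves the detailed procedure to the full protocol. That the nurse is described as uninvolved yet prepares the solutions is a matter of wording.
- **The same people recruit, operate and assess.** The protocol does not say so. Overlap is plausible in this setting but undocumented.
- **12, 24 or 42 allocations are known in advance.** Those counts treat a 2/3 guess like a certainty.

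**Conclusion.** The point holds in a limited form. A disclosed fixed block of 4, combined with unblinding by the study team on suspicion of a listed event, makes some later allocations partly predictable to that team. Under the stated assumptions, the gain at enrolment is about 2, 4 or 8 extra correct guesses among 176 patients at unblinding rates of 5%, 10% or 20%. It would be smaller if unblinding came later or boundaries were not known. This does not undermine the trial; it is a small weakness in concealment that can be reduced at almost no cost. The envelope wording is an ambiguity to settle, not a demonstrated breach.

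**What to change.** For participants not yet enrolled, have the independent researcher issue a new list with randomly varying block sizes (for example 4, 6 and 8). Withhold the sizes from recruiting, operating and assessing staff until database lock. State whether allocations are held as one list or singly, and confirm one sealed code per participant, so that breaking one code never shows another.

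The cost is a short amendment, a regenerated list and, if not already in place, individual code envelopes. A final imbalance of a few patients is possible if recruitment stops within a block. Treatment, endpoints and sample size are unchanged. Predictability is reduced, not removed, since the unblinding that drives it remains. The benefit falls as fewer participants remain to be enrolled.

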### Intervention

On the morning of the surgery, the appointed nurse will prepare Solutions A, B, and C according to the treatment allocation and the patient body weight (Wt, in kilograms) checked with ID number, with 100 ml Solution A as the loading dose, 100 ml Solution B as the maintenance dose, and 250 ml Solution C as the bolus dose. In the tTXA group, Solution A consists of 100 ml 0.9% normal saline (NS), Solution B consists of 100 ml 0.9% NS, and Solution C consists of 500 mg TXA dissolved in 250 ml 0.9% NS. In the ivTXA group, Solution A consists of 10 mg/kg TXA dissolved in 100 ml 0.9% NS, Solution B consists of 20 × Wt (mg) TXA dissolved in 100 ml 0.9% NS, and Solution C consists of 250 ml 0.9% NS. In both groups, Solution A will be infused as a bolus intravenously 15 min prior to operation initiation, Solution B will be infused at 5 ml/h intravenously from operation initiation until the last suture (i.e., 1 mg/kg/h TXA infusion in the ivTXA group), and Solution C will be applied for topical wound irrigation for 5 min with the waste fluid removed by suction before the wound is closed.

### Adverse event management and emergency termination of the study

In this study, AEs include, but are not limited to, deep venous thrombosis, myocardial infarction, pulmonary embolism, cerebrovascular disease, impaired liver function, impaired renal function, incisional hematoma/infection, and convulsive seizures. Patients will be closely monitored during the study period. In case of suspicions for the preceding AEs, the study team will break the blind, and patients will be treated appropriately under the instructions of both spine surgeons and internal medicine physicians. All AEs will be diligently recorded and reported in the final manuscript.

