## Methods/design

### Hypotheses

To investigate the non-inferiority of tTXA to ivTXA in blood conservation and clinical safety, our working hypothesis is that tTXA-treated participants suffer *no more* blood losses or allogeneic transfusions, exhibit *undiminished* postoperative hemoglobin level and coagulation function, and are subject to *no increase* in length of hospital stay (LOH) and adverse event (AE) rate compared with those treated with ivTXA.

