#### Safety outcomes

The nature, incidence, duration, and severity of AEs, discontinuation due to AEs, AEs occurring during and after intervention discontinuation, body weight, 12-lead electrocardiograms (ECGs), physical examinations, and vital signs will be monitored in this study.

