For safety analysis, the AEs and abnormal findings in laboratory tests will be listed with the relationship to the study treatments. Fisher’s exact test will be used to compare the rates of participants who have at least one AE between groups in the SS set.

Statistical analyses will be performed using SPSS version 23.0 software (SPSS Inc., Chicago, IL, USA). A two-sided *p* < 0.05 is considered significant.

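### The adverse-event section makes unblinding mandatory on suspicion of any listed event, wider than the emergency-only exception in the blinding section

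*Protocol article*

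**What the plan says.** Randomization and concealment sets the general rule: "Participants and researchers will all be blinded to the group allocation". Its exception is permissive. At any time during or after surgery a clinician can be unblinded "in case of an apparent or suspected medical emergency".

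The section on adverse event management and emergency termination has its own rule: "In case of suspicions for the preceding AEs, the study team will break the blind". The events it refers to form an open list. Besides thrombotic, cardiac and cerebrovascular events, the list contains "impaired liver function, impaired renal function, incisional hematoma/infection, and convulsive seizures". No threshold of severity or urgency is attached.

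Adverse-event data are used in three places:

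- Safety outcomes monitors "The nature, incidence, duration, and severity of AEs".
- In the safety analysis under Sample size and statistical analysis, "the AEs and abnormal findings in laboratory tests will be listed with the relationship to the study treatments", and Fisher's exact test is used to "compare the rates of participants who have at least one AE between groups in the SS set".
- The working hypothesis under Hypotheses includes no increase "in length of hospital stay (LOH) and adverse event (AE) rate compared with those treated with ivTXA".

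**The concern.** The two rules cannot both be followed for an event that is suspected but not urgent. A moderately raised transaminase or a reddened wound would leave the blind intact under the first rule and would oblige the study team to break it under the second.

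The order of events is what matters. Suspicion is still raised blind. Whether the event is confirmed, how severe it is and whether it is related to treatment may then be decided by someone who knows the arm. The Background section presents systemic harm from intravenous tranexamic acid as the reason for the trial, so expectation could enter those decisions, above all attribution. At stake is the credibility of the safety comparison, which is part of the trial's hypothesis.

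**Working it through.** **The two rules side by side**

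| | Randomization and concealment | Adverse event management |
|---|---|---|
| Trigger | apparent or suspected medical emergency | suspicion of a listed event |
| Force | permitted | required |
| Who is named | any clinician | the study team |

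Acting on suspicion is common to both. What makes the second rule wider is that it has no emergency condition and is mandatory.

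**Where they agree and where they differ**

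- *Agree:* myocardial infarction, pulmonary embolism, stroke, seizure, and an urgent hematoma. The Discussion names spinal epidural hematoma as a risk in this setting.
- *Either, depending on presentation:* deep venous thrombosis.
- *Differ:* impaired liver function, impaired renal function, and non-urgent incisional hematoma or infection.

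**How exposed each item is**

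- Wound events rest most on judgement and are the most exposed.
- Liver and renal events rest on laboratory values and are less exposed. The article gives laboratory limits for these only as exclusion criteria, so some judgement may remain.
- Relationship to treatment is a judgement for every event.
- Total blood loss comes from a hematocrit formula plus any volume transfused. The hematocrit part is largely protected.

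**What it would take to change the test result**

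There is no figure in the plan to reproduce. The article gives no wound, liver or renal event rates and no expected number of code breaks, so the starting counts below are assumptions. Only the lowest has an anchor: 3 per arm is close to 0.03 × 88 = 2.6, using the 3% thromboembolic rate that the Background cites after high-dose intravenous use. That is one event class only.

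Inputs: 88 per arm (Sample size and statistical analysis); two-sided Fisher's exact test; threshold p < 0.05.

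One patient's change of status moves that arm's rate by 1/88 = 1.14 percentage points. Reclassifying an event changes nothing for a patient who has another adverse event.

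From equal counts, I searched every split of removals in one arm and additions in the other for the smallest total giving p < 0.05:

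| Assumed start | Fewest changes | Results reaching p < 0.05 | Additions in one arm only |
|---|---|---|---|
| 3 v 3 | 6 | 0 v 6 (p = 0.029) | 8: 3 v 11 (p = 0.048) |
| 9 v 9 | 8 | 1 v 9 (p = 0.018); 2 v 10 (p = 0.032); 3 v 11 (p = 0.048) | 11: 9 v 20 (p = 0.041) |
| 18 v 18 | 11 | 7 v 18 (p = 0.029); 8 v 19 (p = 0.035); 9 v 20 (p = 0.041); 10 v 21 (p = 0.047) | 13: 18 v 31 (p = 0.043) |

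All the changes must work in the same direction between arms. Creating a false significant difference in this way therefore takes many reclassified patients.

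**The case against.** The strongest reply is that the second rule is only the operational form of the first. Its section heading mentions emergency termination, the same sentence goes on to treatment, and the blinding section already allows unblinding on suspicion. The heading does not limit the operative sentence, however. That sentence covers adverse-event management in general and names events that are often not emergencies.

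A second reply is that bias requires the assessor to learn the arm and act on it, and that a condensed article may leave code-break and assessment procedures to the full protocol. This is fair as far as it goes: the absence of a described blinded assessor is not counted here. The point rests on what is stated, namely a rule that has the study team break the blind.

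A third reply is that generous unblinding for safety is a defensible choice, since the drug is given only during surgery and the primary outcome is largely laboratory-based. That holds for emergencies, where nothing would change. It is weaker for a non-urgent event, where knowing the arm may not alter care.

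Two practical cautions stand. In a single hospital with one surgical team, limiting disclosure to the treating clinician may shield only part of the assessment. Severity also cannot always be settled when an event is first suspected.

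**Conclusion.** The inconsistency is real. As written, the adverse-event rule discloses the arm before confirmation, grading and attribution of non-urgent liver, renal and wound events, and so goes beyond the emergency exception.

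The consequence is modest. Bias is possible but not shown; it depends on the assessor knowing the arm and being influenced by it. Its direction for wound events cannot be predicted and its size cannot be estimated from the document. A false significant difference in the any-event rate would need at least 6 to 11 arm-dependent changes across the assumed starting counts. The more realistic effect is a shift of a percentage point or so per reclassified patient in the reported rates, together with a less reliable listing of relationship to treatment. This is a point to consider and does not threaten the primary analysis.

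**What to change.** Bring the adverse-event section into line with Randomization and concealment. On suspicion of a listed event, the code is opened only when knowing the arm is needed for the patient's urgent care, and it is disclosed only to the treating clinician. Where care allows, onset, severity and relationship to treatment are recorded before the code is opened.

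The cost is one sentence and slightly more documentation. Emergency access stays as it is, and the appointed nurse already holds the codes. The trial was recruiting when the article was published. If the sponsor regards the change as a significant modification, the article's own rule on informing investigators, participants and the registry applies.

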### Outcomes

#### Primary outcome

The primary outcome of this study will be the perioperative total blood loss (TBL), which is the accumulation of the gross blood losses since operation initiation until postoperative day 3 (POD3). TBL is calculated using the formula provided by Gross [16]:$$ \mathrm{Total}\ \mathrm{blood}\ \mathrm{loss}=\mathrm{PBV}\times \left({\mathrm{Hct}}_{\mathrm{pre}}-{\mathrm{Hct}}_{\mathrm{post}}\right)/{\mathrm{Hct}}_{\mathrm{ave}} $$where PBV refers to the patient’s blood volume, Hct_pre_ is the initial preoperative hematocrit, Hct_post_ is the hematocrit on POD3, and Hct_ave_ is the average of the Hct_pre_ and the Hct_post_.

PBV is then calculated using the formula proposed by Nadler et al. [17]:$$ \mathrm{PBV}={\mathrm{k}}_1\times \mathrm{height}{\left(\mathrm{m}\right)}^3+{\mathrm{k}}_2\times \mathrm{weight}\ \left(\mathrm{kg}\right)+{\mathrm{k}}_3 $$where k_1_ = 0.3669, k_2_ = 0.03219, and k_3_ = 0.6041 for men, and k_1_ = 0.3561, k_2_ = 0.03308, and k_3_ = 0.1833 for women.

#### Secondary outcomes

Secondary outcomes include:Visible blood losses (intraoperative, postoperative 0–24 h, postoperative 0–48 h, combined perioperative blood loss) and postoperative hidden blood loss (HBL)Postoperative conventional coagulation monitoring indices: PT, APTT, fiber Bragg grating (Fbg), INR, and TEG monitoring indices: reaction time (R time), clot formation time (K time), clot strength (MA), fibrinolysis (LY30)Postoperative hemoglobin nadir (within postoperative 48 h)Perioperative transfusion amounts and ratesPlasma TXA levels tested with solid phase microextraction technique (SPME) [18] 5 min after the last suture (t_4_) and on postoperative day 1 (POD1, t_5_).LOH

Among the preceding indices, combined visible perioperative blood loss refers to the gross visible blood loss since operation initiation until postoperative 48 h. Two pretrained surgeons will take charge of the visible blood loss assessments. Specifically, for intraoperative visible blood loss, it is calculated by weighing surgical sponges, measuring blood collected by suction canisters, and subtracting all irrigations fluids added to the surgical field. For postoperative visible blood losses, since the drainage fluid in the Hemovac includes not only blood but also tissue fluid exudation [19], the actual postoperative blood loss (PBL) will be calculated using our previously reported formula [20]:$$ {\mathrm{PBL}}_{24\mathrm{h}\;\left(48\mathrm{h}\right)}=\mathrm{volume}\ {\mathrm{of}\ \mathrm{drainage}}_{24h\;(48h)}\times {\mathrm{Hct}}_{24\mathrm{h}\left(48\mathrm{h}\right)}/{\mathrm{Hct}}_{\mathrm{ave}} $$where Hct_24h(48h)_ refers to the drainage Hct level tested 24 h or 48 h postoperatively. HBL is also calculated by subtracting the combined visible perioperative blood loss from TBL. All blood losses are determined on the basis of milliliters. If allogeneic transfusion is performed, then TBL is equal to the loss calculated from Hct changes plus the volume transfused.

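### Hidden blood loss is a total to POD3 minus visible loss to 48 h, so any blood drained in between is counted as hidden

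*Protocol article*

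**What the plan says.** The Primary outcome section of the protocol article defines TBL as the "accumulation of the gross blood losses since operation initiation until postoperative day 3". The closing value in its formula "is the hematocrit on POD3".

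The Secondary outcomes section gives visible loss an earlier end: "combined visible perioperative blood loss refers to the gross visible blood loss since operation initiation until postoperative 48 h". The drain measurements match that end, since the hematocrit used to correct drain volume "refers to the drainage Hct level tested 24 h or 48 h postoperatively". The same paragraph then states that "HBL is also calculated by subtracting the combined visible perioperative blood loss from TBL".

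The text shown does not say when drains are removed, describes no drain reading after 48 h, and makes no adjustment for the different end times. The Discussion explains the POD3 hematocrit as a steady-state value for calculating TBL; it does not take up the subtraction.

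**The concern.** A residual such as HBL means what its name says only if both terms cover the same period. Here the minuend covers a longer period than the subtrahend, so blood that leaves through the drain after 48 h lowers the POD3 hematocrit, enters TBL, is never subtracted, and is reported as hidden although it was visible.

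HBL is not a minor item in this trial. The Discussion presents it as a quantity not previously studied with topical TXA, links it to complications and length of stay, and sets it beside hidden-loss shares of 39–47% of TBL from other series. If it contains unmeasured drainage, both its level and its share of TBL are overstated by that amount, and comparison with other series is harder to interpret.

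**Working it through.** The plan states no figure for HBL that could be reproduced. The check is an identity followed by an illustration of scale.

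**Identity.** Write V(a, b) for visible loss between times a and b.

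- Plan: HBL(reported) = TBL(0, POD3) − V(0, 48 h)
- Matched windows: HBL(matched) = TBL(0, POD3) − V(0, POD3)
- Since V(0, POD3) = V(0, 48 h) + V(48 h, POD3), it follows that HBL(reported) = HBL(matched) + V(48 h, POD3).

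The excess is exactly the visible loss after 48 h. It is zero for a participant who loses nothing visible after 48 h, for example because the drain is already out.

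**Between arms.** Taking the difference of arm means (tTXA minus ivTXA) gives

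difference in HBL(reported) = difference in HBL(matched) + difference in V(48 h, POD3).

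Equal late drainage cancels from the comparison but still raises the HBL level in both arms. Unequal late drainage passes one-for-one into the HBL difference.

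**Inputs for scale.**

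- Expected TBL: 971 ml (tTXA) and 911 ml (ivTXA), from Sample size and statistical analysis.
- HBL share of TBL: 39% to 47%, from the Discussion.
- V(48 h, POD3): not in the document. Assumed 0–90 ml of blood. The upper end is 150 ml of drain fluid at a drain-to-blood hematocrit ratio of 0.6, both assumed: 150 × 0.6 = 90 ml.

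**Expected HBL.** Lowest: 0.39 × 911 = 355 ml. Highest: 0.47 × 971 = 456 ml.

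**Share of HBL that would be late visible loss.**

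| Assumed V(48 h, POD3) | divided by 456 ml | divided by 355 ml |
|---|---|---|
| 0 ml | 0% | 0% |
| 25 ml | 5% | 7% |
| 50 ml | 11% | 14% |
| 90 ml | 20% | 25% |

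The 25% pairs the largest assumed late loss with the smallest expected HBL, so it is the edge of the range and not a central estimate. The 39–47% shares come from cited series whose own measurement windows are not shown here.

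**The case against.** The strongest reply is that the gap may be empty. Drain readings stop at 48 h and the sum to that time is called the combined perioperative loss, which fits drains being out by about then. Drain timing is also a detail that an article may leave to the full protocol, and the assessment schedule (Fig. 1) is not shown. This stands as far as size goes: no error can be shown to occur. It does not repair the formula, which as written joins two windows without stating the condition that would make them equivalent. One sign points the other way: the Abstract lists total postoperative blood loss separately from the 0–48 h loss, which would be redundant if visible loss always ended at 48 h. That is suggestive only, and the item does not reappear in the list under Secondary outcomes.

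A second reply is that the later hematocrit has a stated reason, the steady state on POD3. That explains why TBL ends when it does, but not why visible loss ending earlier is subtracted from it.

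Stronger readings are tempting, and the document does not support them:

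- A reader might infer that the arms are biased against each other, because the infusion stops at the last suture while the topical drug is applied just before closure. The Intervention section describes a 5-minute irrigation with the fluid then suctioned off, and nothing shows that drainage after 48 h differs by arm. The route for bias is real; the bias is conjecture.
- A reader might infer that visible loss is understated. It is defined as ending at 48 h and measures what it says.
- A reader might extend the criticism to the hemoglobin nadir, which also ends at 48 h. That is a clearly labelled outcome, it does not enter HBL, and it contradicts nothing.

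**Conclusion.** The point holds as a defect in the definition of one secondary outcome. As written, reported HBL is hidden loss plus any visible loss between 48 h and the POD3 sample. That conclusion needs no assumption beyond the two stated windows.

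The amount cannot be determined from the document. It is nil where drains are out by 48 h, and up to about 25% of HBL under the assumed 0–90 ml of late drain blood and an HBL of 355–456 ml. The primary outcome TBL, the non-inferiority test and the 0–24 h and 0–48 h visible-loss outcomes are unaffected. The correction is worth making because HBL is a highlighted outcome and the change is small.

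**What to change.** For the HBL calculation only, subtract intraoperative loss plus hematocrit-corrected drain loss up to the POD3 blood sample, or up to drain removal if that is earlier. Where a drain is still in at 48 h, record one further drain volume and drain hematocrit at the end of that window and apply the existing drainage formula. Keep the 0–24 h and 0–48 h visible-loss outcomes as defined. This concerns measurement only and asks for no change in how drains are managed.

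The trial is already recruiting. For participants treated without the later reading, label HBL as including any visible loss after 48 h, and report how many had a drain in place past 48 h. If the records show that none did, one sentence saying so closes the matter and the calculation is unchanged.

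The cost is one extra drain reading in some patients, one line in the outcome definition, and a mixed HBL definition between those already treated and those still to come. The POD3 blood sample is already taken.
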